### Standardisation of assessments

Blinded assessors have systematically undergone competency training to ensure standardisation of data collection methods. This included theoretical learning about the assessments, demonstration and practice on volunteers (patients with stroke in our rehabilitation hospital) under the supervision of the study’s clinical research coordinators. The success of blinding will be formally tested by asking the outcome assessors to guess the study group assignment of patients after the end of the study period and comparing these responses to what would we expect by chance.

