**Fig. 1 Fig1:**
[figure not shown]
*Flow diagram* of study design

The study is conducted at the neurological rehabilitation hospital Asklepioskliniken Schildautal Seesen in Germany. Before the intervention, patients will be randomised in a 1:1 ratio into one of two intervention parallel groups.

The first experimental group will receive, in addition to standard treatment, intensive upper limb strength training with an intensity of 80% of the maximum force (three times per week, over three weeks, 60 min per session, with a total of nine additional sessions). The other group will receive, in addition to standard treatment, functional arm training with an intensity of 40% of the maximum force (with the same quantity, frequency and treatment time as the intervention group). After receiving ethical approval and registration of the study, we started recruiting in our hospital in May 2017. The final assessments will be made in 2018. The study protocol is prepared according to the SPIRIT Statement (http://www.spirit-statement.org/) [27] (see Additional file 1; for the SPIRIT figure, see Fig. 2).

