### Sample size

Based on the study by da Silva et al., we assume a mean difference of 10 kg in the intervention group and a mean difference of 8 kg in the control group with a standard deviation (SD) of 3 kg [11]. We assume an alpha level of 5% and a statistical power of 80% (beta = 20%) using a two-sample t test for mean differences. We used the G*Power Version 3.1.9.2 power and sample size programme of the university of Kiel, Germany for our sample size calculation (‘G*Power’, 1992–2014). According to the programme, we will need 37 patients per study arm. Because we expect a 5% dropout rate, a total of 78 patients (39 per study arm) would be enrolled to ensure 37 individuals in both intervention arms.

Sample size calculations can be based on clinical meaningful differences, on between-group comparisons of similar studies or conveniently on both.

The study by Lang et al. is the only one which examined the minimal clinical important difference of grip strength; its results are limited by a small sample size and wide standard deviations [33]. There are no further studies which verified these results.

Because of these limitations we decided to use the results of another study which assessed between-group differences in grip strength after upper limb strength training [6].

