### Statistical methods

We will conduct both intention-to-treat and per-protocol analyses, with the intention-to-treat analysis being always the primary analysis for the primary and secondary outcomes.

Our descriptive statistics will include means and SD for continuous variables, and the number and proportions for categorical variables as appropriate [43]. We will compare the two intervention groups at baseline regarding characteristics and demographics, using two-tailed Student’s t tests or Fisher’s exact tests, as appropriate. The alpha level will be set to 0.05 for all comparisons. To avoid multiplicity, we will use a Bonferroni alpha adjustment for multiple comparisons of the same outcome. Skewed data will be analysed with non-parametric test alternatives (e.g. we will use the Mann–Whitney U test instead of Student’s t tests if data are skewed). For the primary endpoint, the grip strength, we will test the hypothesis that there is a significant difference after three weeks of intervention between groups. We will consider a minimum difference of 5 kg of the grip strength between groups as being clinically important [44]. We will use IBM SPSS Statistics Version 23.0.0.0 for all statistical procedures (IBM Corporation, Armonk, NY, USA). No interim analysis will be conducted.

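### A non-significant comparison of about 74 to 78 assessor guesses with chance cannot show that blinding succeeded; report the proportion correct with a confidence interval instead

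*Protocol article*

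**What the plan says.** The check is described in one sentence of the protocol article, under Standardisation of assessments: "The success of blinding will be formally tested by asking the outcome assessors to guess the study group assignment of patients". The guesses are requested after the study period ends, and the method is "comparing these responses to what would we expect by chance". No test, sidedness, estimate or tolerable degree of unblinding is named.

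Three other places set the size of the check:

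- Study design: "patients will be randomised in a 1:1 ratio", so chance is 50% correct.
- Sample size: "a total of 78 patients (39 per study arm) would be enrolled to ensure 37 individuals in both intervention arms", so there are at most 78 guesses at one per patient, and about 74 if the expected dropouts yield none.
- Statistical methods: "The alpha level will be set to 0.05 for all comparisons".

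**The concern.** A test of whether guesses differ from chance can produce evidence against blinding. It cannot by itself produce evidence for it. When such a test is called a formal test of the success of blinding, a non-significant result will naturally be read as success. With this few guesses, non-significance is compatible both with good blinding and with a blind that leaked for a meaningful minority of patients.

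The check matters here. Patients and therapists are told the allocation (Randomisation and concealment of allocation), so the assessor is the blinded party when outcomes are measured. The primary endpoint, dynamometer grip strength, depends on the patient's effort. The article also names non-blinded assessors as a limitation of an earlier trial (Background and Discussion). If non-significance were reported as successful blinding, readers might set aside an assessor bias that the data had not excluded.

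**Working it through.** **Number of guesses.** The plan's sample size reproduces. "we assume a mean difference of 10 kg in the intervention group and a mean difference of 8 kg in the control group" gives a difference of 2 kg; with an SD of 3 kg the standardised difference is 2/3 = 0.667. A two-sided t test at 5% with 80% power needs 36.3, rounded up to 37 per arm (power 0.808). With 5% dropout, 37/0.95 = 38.9, or 39 per arm and 78 in total. The range for the guesses is therefore n = 74 (2 × 37) to n = 78 (2 × 39).

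**Link between leak and correct guesses.** If assessors know the allocation for a fraction k of patients and guess the rest at random, the proportion correct is p = k + (1 − k)/2 = 0.5 + k/2. So k = 10% gives 55% correct, 20% gives 60%, 30% gives 65% and 40% gives 70%.

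**Test.** X, the number correct, is binomial(n, p), and the null is p = 0.5. The two-sided exact test takes the smallest r with P(X ≥ r | 0.5) ≤ 0.025 and rejects at X ≥ r or X ≤ n − r.

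- n = 74: r = 46 (actual size 4.7%)
- n = 78: r = 49 (actual size 3.1%)

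The one-sided test uses 0.05 in the upper tail: r = 45 at n = 74 (size 4.0%) and r = 47 at n = 78 (size 4.4%).

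Miss rate = 1 − P(reject | p):

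| True correct | Allocation known | Two-sided, n=74 | Two-sided, n=78 | One-sided, n=74 | One-sided, n=78 |
|---|---|---|---|---|---|
| 55% | 10% | 87% | 90% | 81% | 79% |
| 60% | 20% | 60% | 65% | 51% | 47% |
| 65% | 30% | 26% | 30% | 19% | 16% |
| 70% | 40% | 6% | 7% | 3% | 3% |

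The two-sided test reaches 50% power at 61.4% correct (n = 74) or 62.1% (n = 78), which is about 23% to 24% of patients known. It reaches 80% power at about 66% to 67% correct. By the normal approximation, 80% power at 60% correct would need about (1.96 × 0.5 + 0.842 × √0.24)² / 0.1² = 194 guesses.

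**What a non-significant result leaves open** (exact 95% intervals):

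- Largest non-significant count: 45/74 = 60.8%, interval 48.8% to 72.0%; 48/78 = 61.5%, interval 49.8% to 72.3%.
- Exactly half correct: 37/74, interval 38.1% to 61.9%; 39/78, interval 38.5% to 61.5%.

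An upper limit of 72% corresponds to k = 2 × 0.72 − 1 = 44% of patients known. That is the edge of the interval for the most extreme non-significant result, not a typical value.

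**Sensitivity.** A 2×2 table of guess by arm gives a similar picture. At 60% correct the miss rate is 65% (Fisher) or 56% (chi-square) with 39 per arm, and 69% or 60% with 37 per arm. If 'don't know' answers left only 62 or 55 usable guesses, the two-sided miss rate would be 72% or 75% at 60% correct, and 41% or 47% at 65%.

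**The case against.** The strongest objection is that the article writes down no decision rule. It does not say that p > 0.05 means success, it names no test, and the alpha sentence stands among the baseline and outcome comparisons without mentioning the guesses. That is correct. A reader might infer a stated pass rule, but reading non-significance as success is only the natural sense of formally testing success against chance.

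A second tempting inference is that the check misses any real leak more often than not. The figures do not support that. Two-sided, it holds only up to about 61% to 62% correct. A one-sided test is a reasonable choice, since a leak pushes guesses above chance, and at n = 78 it finds the 60% case slightly more often than it misses it. A gross failure of the blind would nearly always be detected.

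Third, an unseen analysis plan may add an estimate and interval. It may, and the lack of that detail is not the point. The point is the criterion the article does state, which cannot support the conclusion attached to it.

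Finally, neither the sample size nor the efficacy analysis depends on this check. That limits the consequence to how the trial's blinding is reported and believed.

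**Conclusion.** The concern holds in a limited form. At 74 to 78 guesses, a non-significant comparison with chance does not show that the assessors were blind. Modest leaks, up to about 60% correct, are missed in roughly 60% to 90% of cases two-sided, and at 60% correct in about half of cases one-sided. Even the least favourable non-significant result is compatible with about 72% correct. Larger leaks are mostly detected.

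These figures assume one independent guess per patient, the same rate of correct guesses in both arms, no 'don't know' answers, and that alpha 0.05 applies to this test. None of these is stated for the guesses. The leak sizes are illustrations, since the article gives no expected rate. The interval argument does not depend on any assumed leak size.

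**What to change.** In Standardisation of assessments, replace the test of success with an estimate. Suggested wording: *We will report the proportion of correct guesses (or a blinding index), overall and by arm, with 95% confidence intervals. A non-significant difference from chance will not be taken as evidence of successful blinding.*

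No pass/fail margin is needed, and one would have a price. If blinding were declared successful only when the upper limit fell below 65% correct, a perfectly blinded trial would qualify only about 71% to 72% of the time.

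The change costs wording only, because the guesses are already planned. The small downside is that the trial may be unable to claim that blinding was shown to be successful. With a half-width of about 11 percentage points (1.96 × √(0.25/78) = 0.111; 0.114 at n = 74), that reflects what the data can support.

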### Data collection

Pseudonymised outcome data are collected by blinded assessors at baseline (t0) and after three weeks of therapy (t1) (see Fig. 2). Pseudonymised outcome data will be entered in a spreadsheet by a masked researcher who has no knowledge of identifiable participant information or treatment assignment.

### Randomisation and concealment of allocation

Each study participant will be randomly assigned to one of two intervention groups, either the low-intensity training group or the high-intensity training group. Allocation will be concealed within an opaque sealed envelope. The computer-generated random allocation sequence list will be carried out using a random-number generator (randomizer.org). Assignments will be enclosed in sequentially numbered, opaque, sealed envelopes and stored at the central study centre. The persons who assess eligibility, obtain informed consent and enrol patients in the trial (SH, CH) have no knowledge of group assignment (Fig. 2). After recruitment and after the initial assessment, the appropriate numbered, opaque, sealed envelope will be opened and the randomisation information will be given to the patient and therapists (but not to the outcome assessors). We will not include further potential covariates in our stratification. However, we will test the influence of different covariates statistically on the main effect of the primary outcome.

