Chan et al. found in a single-group cohort study that weight-supported training with robotic devices can increase arm function, especially in subacute stroke patients with moderate or severe impairments [9]. The more severely affected the patients, the higher the improvements. It is unclear if robotic arm training has an advantage to another intervention type because there is no comparison group. The training effects are different in patients with mild, moderate, or severe impairments but we do not know if all these patients can train with additional weights, no matter how severe the impairments are.

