Randomised controlled trials (RCT) found that resistance training for the upper limb that uses additional weights for a higher training intensity increased strength [10, 11], arm function [12–15] and arm activities [14] in chronic stroke patients. Three studies searched for adverse events (AE) after arm strength training in chronic stroke patients. Two of these found no AEs [16, 17] and one reported muscle soreness [15]. Only two studies examined treatment effects of such intensive and progressive arm training in subacute stroke patients [17, 18]. Donaldson et al. found that additional functional resistance training leads to greater improvements of arm function than standard treatment or double dose of standard treatment [18]. In this pretest–post-test clinical trial, no between-group comparisons were performed. Thus, there is no information about a possible advantage for one of the interventions in subacute stroke patients. Winstein et al. compared a control group which performed five times per week functional training with an intervention group which performed a combination of three times resistance training and two times functional training per week [19]. Mild affected stroke patients of the intervention group showed greater improvements of arm function (measured with the motor subscore of the Fugl-Meyer-Assessment for upper extremity) than the control group. There were no group differences in other functional assessments, e.g. grip strength. This study is limited by non-blinded assessors. Only these two studies investigated resistance training with additional weights in the first three month after stroke. AEs in patients in the subacute phase after stroke were not examined. This evidence related to the effectiveness of strength training (resistance training) in improving upper limb function and activities is insufficient. A solid evaluation of intensive resistance arm training in the subacute phase after stroke is not possible. It is important to investigate common interventions early after stroke to follow the recommendations of an early start to the training. An early start to the training (one week after stroke onset) with higher treatment dose speeds up the functional recovery of arm activities [20, 21]. The highest rise of recovery is achieved in the first weeks after stroke with the major part of recovery already reached at this point [20, 22]. However, less is known about which therapeutic interventions could support this early recovery. Strength training for preservation or improvement of muscle strength is recommended in stroke guidelines [23, 24]. Despite the lack of evidence for therapeutic effects and AEs in subacute and early chronic stroke patients, resistance training is recommended [25] and used in rehabilitation.

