### Eligibility criteria

The diagnosis of stroke will be confirmed by a neurologist before admission to our neurological rehabilitation hospital. A previous stroke is no reason for exclusion. Participants will be in the subacute phase (within three months after stroke) and will have a Barthel Index (BI) of at least 30 points. If the BI is 85–100 points (mild stroke), the patient will be included at least 24 h after stroke. If the BI is < 85 points (moderate stroke) the patient will be included at least seven days after stroke. They will be able to sit free for 30 s (sitting balance score of at least 2 points) and they will be able to lift the affected hand from their lap to a desk standing in front of them. They will have a Medical Research Council Score of 2–4 for shoulder abduction, elbow and finger flexion. The passive range of motion (ROM) will allow a touch of finger tips and thumb as well as submaximal finger extension. Patients will achieve an Apraxia Screen of TULIA Score of ≥ 5 (for details, see Table 1).

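### The primary grip-strength comparison is planned unadjusted and the covariates to be tested are unnamed, although the protocol describes recovery as dependent on time since stroke; a fixed adjusted model would recover precision at almost no cost

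*Protocol article*

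**What the plan says.** **Allocation** (Protocol article, Randomisation and concealment of allocation). The sequence is described in one sentence: "The computer-generated random allocation sequence list will be carried out using a random-number generator (randomizer.org"). The section then says: "We will not include further potential covariates in our stratification". No stratification factor is named in that section or elsewhere, so the words *further* and *our stratification* point to nothing described. The next sentence announces that "we will test the influence of different covariates statistically on the main effect of the primary outcome", without naming a covariate or a model.

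**Analysis.** The Sample size section uses a two-sample t test for mean differences. Statistical methods names Student's t test, with Mann–Whitney for skewed data, and states the primary hypothesis as a between-group difference after three weeks. Neither section carries a covariate.

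**Prognosis** (Background). "The highest rise of recovery is achieved in the first weeks after stroke with the major part of recovery already reached at this point". Of a cited single-group robotic-training cohort it says: "The training effects are different in patients with mild, moderate, or severe impairments".

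**Entry window** (Eligibility criteria). "Participants will be in the subacute phase (within three months after stroke"). The earliest entry is 24 hours for a Barthel Index of 85–100 and seven days for an index below 85; the minimum index is 30. Time since onset and Barthel Index are both on the list of recorded baseline data (Additional information).

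**The concern.** The primary outcome is read three weeks after baseline in patients who may start anywhere from the first days to three months after stroke. If recovery is steepest early, as the Background says, early and late entrants can have the same baseline grip and different expected gains. With 39 per arm, one arm may by chance hold more early entrants. Nothing in the allocation limits this, and the named tests do not correct for it. Baseline significance tests, which Statistical methods does plan, can flag an imbalance but do not remove it.

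The promise to test covariates leaves open which of the many recorded variables are used, and whether the result changes the primary estimate. At stake are the precision of the estimate and the credibility of any adjustment chosen after the data are seen.

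**Working it through.** **Inputs from the Sample size section.** Mean changes of 10 and 8 kg, so a difference of 2 kg; SD 3 kg; alpha 5%; power 80%; 37 per arm analysed; 39 per arm enrolled after 5% dropout.

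**Not in the documents.** The correlation r between time since onset and three-week grip gain. I take r = 0.3 and 0.5 as assumptions.

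**1. The plan's own figure.** A two-sided t test with standardised difference 2/3 needs 36.3 per arm, rounded up to 37. Power at 37 is 80.8%. Inflated for 5% dropout this gives 39 per arm and 78 in total. The stated figures reproduce.

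**2. Total chance variation already allowed for.** Standard error of the difference = 3 × √(2/37) = 0.70 kg, so the 95% range is ±1.96 × 0.70 = ±1.37 kg. Imbalance in a prognostic factor is part of this range, not an addition to it, as long as the 3 kg SD already includes the recovery variance.

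**3. The part due to time since onset.** SD of the chance shift with 39 randomised per arm = r × 3 × √(2/39).
- r = 0.3: 0.204 kg; × 1.96 = 0.40 kg, which is 20% of 2 kg.
- r = 0.5: 0.340 kg; × 1.96 = 0.67 kg, which is 33% of 2 kg.

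One trial in 20 is shifted by more than this, in one direction or the other.

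**4. Power after adjustment.** Residual SD = 3 × √(1 − r²), 37 per arm.

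| Assumed r | Residual SD (kg) | Power |
|---|---|---|
| 0 (unadjusted) | 3.00 | 81% |
| 0.3 | 2.86 | 84% |
| 0.5 | 2.60 | 90% |

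**5. Does stratification or adjustment bring the gain?** A simulation with 8,000 trials per setting used 37 per arm and one two-class factor held by half the patients. The factor explained 25% of the variance (r = 0.5).

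| Allocation | Analysis | Type I error | Power |
|---|---|---|---|
| Unstratified | Unadjusted | 5.2% | 81% |
| Unstratified | Adjusted | 5.1% | 90% |
| Stratified | Unadjusted | 2.4% | 84% |
| Stratified | Adjusted | 5.1% | 91% |

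Adjustment brings nearly all of the gain. Stratifying adds about one point of power once the model is adjusted, and without adjustment it makes the t test conservative.

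**6. If the 3 kg SD is too small.** The SD comes from a study that the Background lists among trials in chronic stroke. Suppose subacute recovery adds an SD of 2 kg (assumption). The total SD is then √(9 + 4) = 3.61 kg and unadjusted power falls to 65%. The documents neither confirm nor exclude this.

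**The case against.** The strongest reply has three parts.

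*The protocol already promises covariate analysis.* It does, time since onset and Barthel Index are recorded, and an article may leave the covariate list to an analysis plan that is not shown. That stands as a reason not to fault the missing list alone. But testing the influence of covariates is not an adjusted primary analysis fixed in advance, and the tests the article does name cannot carry covariates. That is a choice made in the text, and a better one is available.

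*Unstratified randomisation is valid.* This stands in full. A reader might infer that chance imbalance can mimic or hide much of the 2 kg effect. The documents do not support that. Type I error stays near 5%, and the shift lies inside the ordinary ±1.37 kg as far as the SD holds. Under the assumptions used here it reaches 20–33% of 2 kg in only 1 trial in 20. Nor do the documents say that the grip gain is driven mainly by the time of entry: the Background speaks of recovery in the context of arm activities, its severity evidence is a cohort without a comparison group, and r = 0.3 to 0.5 means 9–25% of the variance.

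*Changing the allocation now is not free.* This also stands. The trial is single-centre, recruitment began in May 2017, and patients and therapists learn the allocation. Stratified blocks introduced midway would have to be reported as a second phase and would make assignments easier to predict.

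A reader might also infer that the lack of described blocking defeats the aim that 78 patients "would be enrolled to ensure 37 individuals in both intervention arms". The article does not say that the list is unrestricted. Even if it were, a 33/45 split would still give 82% power.

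**Conclusion.** The point holds as a matter of efficiency and pre-specification, not of bias. The stratification sentence refers to a scheme that is not described, the covariates are unnamed, and the named primary tests ignore factors that the protocol itself treats as prognostic and already records.

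Under the assumed r of 0.3 to 0.5, adjustment gives 3 to 9 percentage points of power at 37 per arm (81% to 84–90%) and removes a chance shift whose 95% limit is 0.40 to 0.67 kg. These sizes rest on r, which the documents do not give, and on the SD of 3 kg holding in subacute patients. A weaker correlation gives a smaller gain. The direction of the recommendation does not depend on the exact value, because adjusting for a few pre-specified baseline variables costs little even if r is small. The change is worth making, but the trial is not invalid without it.

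**What to change.** 1. In Statistical methods, replace the unadjusted primary test with one linear model for three-week grip strength of the affected hand. Terms: treatment group, baseline grip strength, time since stroke onset and Barthel Index. State the scale on which each covariate enters, and fix the model before unblinding.
2. Keep the t test or Mann–Whitney test as a sensitivity analysis.
3. In Randomisation and concealment of allocation, replace the open promise to test covariates with a reference to this model. If allocation is not stratified, say so plainly; if it is, name the factor and add it to the model.
4. Stratified allocation for envelopes not yet opened is optional. If it is adopted, the stratum must be in the primary model.

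**Cost.** One analysis sentence and three degrees of freedom (with 74 analysed, residual degrees of freedom fall from 72 to 69). All the variables are already collected, so no patient contact or extra data are needed, and the change can be made whatever the state of recruitment, provided it comes before unblinding.
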